### 1.2 Aim and hypotheses

The aim of the current study is to investigate feasibility, acceptability and potential indications of treatment effect of group RFCBT in the treatment of young people with psychosis spectrum disorders that display symptoms of rumination.

We hypothesize that 1) group RFCBT will be feasible and acceptable for young people with a psychosis spectrum disorder undergoing OPUS treatment 2) RFCBT will decrease negative symptoms, depressive symptoms, rumination behaviour, and increase level of functioning.

We will use the knowledge generated by the present study in the design of a possible subsequent larger fully powered definitive randomized trial.

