### 2.3 Sample size

As the overall purpose of the study is to uncover acceptability, feasibility and provide indications of a possible treatment effect. the number of subjects is not based on a calculation of statistical power, but rather on an expectation of how many will be able to include over a project period of 18 months A total of 30 patients receiving the intervention will be compared to 30 receiving standard treatment. A sample size of 30 participants is considered adequate for a pilot-study assessing feasibility, acceptability, and providing indications of efficacy of an intervention [36].

The study is situated at Mental Health Center Glostrup, which has approximately 300 active OPUS patients. In previous trials with group-based CBT in OPUS, it has been possible to recruit a minimum of 10% of the total OPUS sample, thus it is realistic to include the 60 patients in a project period of 18-months.

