### 2.4 Randomization

The randomization is done via the computerized randomization function in Research Electronic Data Capture (REDCap) [37] tool in ratio 1:1 on the basis of an uploaded block randomization list (block size 4–6) generated by an external party. In addition, stratification is used to ensure equal distribution of gender between the groups.

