## 6. Analyses

### 6.1 Quantitative analysis

Treatment effect will be analyzed as changes in outcome measures from baseline to post-treatment in the RFCBT group using paired samples t-tests or a corresponding non-parametric test such as Pearson’s chi-square test. Continuous data are presented as mean ± standard deviation (SD). A two-sided significance level of p <0.05 is used.

The estimated pooled standard deviation from both groups in this pilot study will be used to inform the sample size calculation for a fully powered RCT.

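### Section 6.1 judges treatment effect by p<0.05 on change within the RFCBT arm of an unpowered pilot, where a between-arm estimate with its 95% confidence interval would answer the question better

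*Protocol article*

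**What the plan says.** Section 6.1 defines the analysis of treatment effect as change from baseline to post-treatment "in the RFCBT group using paired samples t-tests or a corresponding non-parametric test such as Pearson’s chi-square test". It then states: "A two-sided significance level of p <0.05 is used". Nothing limits that level to one outcome. The only presentation it names for continuous data is mean with standard deviation.

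Section 5.2 lists seven scales: BNSS as the single primary outcome, and PTQ, RRS, SAPS, SFS, CDS and BRIEF as secondary outcomes.

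Section 2.3 states that "the number of subjects is not based on a calculation of statistical power", and gives the purpose as acceptability, feasibility and indications of a possible effect. It also announces a comparison of arms: "A total of 30 patients receiving the intervention will be compared to 30 receiving standard treatment". The Abstract likewise promises a comparison of changes between RFCBT and usual treatment. Section 1.2 words the second hypothesis as a directional prediction: "RFCBT will decrease negative symptoms, depressive symptoms, rumination behaviour, and increase level of functioning".

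**The concern.** A significance criterion does not suit a study that was deliberately not sized for testing. The pilot's question about efficacy is how large the effect might be and how uncertain that is. A p-value at this sample size answers neither part.

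The criterion is also attached to the wrong contrast. A paired test within the RFCBT arm detects change from any cause: ongoing OPUS treatment, natural course, or regression to the mean. The last is to be expected for PTQ at least, because section 2.2 requires a PTQ score of at least 30 at entry. Randomisation protects only the comparison between arms, and section 6.1 specifies no test or estimate for that comparison.

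At stake is how the pilot's efficacy results are read. Section 1.2 says that what is learned will feed the design of a possible larger trial, and section 10 describes the result as an indication of effect to be confirmed later. A significant within-arm change could be taken as such an indication when RFCBT contributed nothing. If the arms were compared by the same criterion, a non-significant result could be taken as absence of effect when the study could not have shown one.

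**Working it through.** **Inputs from the protocol article.** Two-sided alpha 0.05 (section 6.1); 30 per arm, 1:1 (sections 2.3 and 2.4); seven efficacy scales, one of them primary (section 5.2). The plan states no power, effect size or outcome SD, so it has no sample-size calculation to reproduce. The total of 60 is 30 + 30, set by expected recruitment.

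**Assumptions.** Effect sizes, correlations between scales, and 24 per arm as a sensitivity case. The last borrows the 80% therapy-completion target of section 5.1 (0.80 × 30 = 24) as if it were assessment retention.

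**1. The test as written: paired t-test, RFCBT arm, n = 30.** The mean change is expressed in SDs of change (dz). The noncentrality is dz × √n, with 29 degrees of freedom and critical value 2.045.

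- If dz = 0.5 arises under OPUS alone, the noncentrality is 0.5 × √30 = 2.74 and the probability of p<0.05 is 75% with no treatment effect.
- At other values of dz: 0.2 gives 18%, 0.3 gives 36%, 0.4 gives 56%, 0.6 gives 89%.
- With n = 24, dz = 0.5 gives 65%.
- This test has 80% power at dz = 0.53 (0.60 with n = 24), but power for change over time, whatever its cause.

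**2. The announced comparison, if tested at p<0.05: two-sample t-test, 30 per arm.** The noncentrality is d × √(n/2), with 58 degrees of freedom and critical value 2.002.

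| Assumed d | Power, 30 per arm | Power, 24 per arm |
|---|---|---|
| 0.2 | 12% | 10% |
| 0.3 | 21% | 17% |
| 0.4 | 33% | 27% |
| 0.5 | 48% | 40% |
| 0.6 | 63% | 53% |
| 0.8 | 86% | 77% |

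For d = 0.4 the noncentrality is 0.4 × √15 = 1.55. Power of 80% needs d ≈ 0.74 at 30 per arm and 0.83 at 24 per arm.

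**3. Several scales at an unadjusted 0.05, none truly different.**

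- BNSS alone: 5%.
- At least one of seven, independent: 1 − 0.95^7 = 30.2%.
- At least one of seven, simulated with equal correlations of 0.3, 0.5 and 0.7: 27%, 23% and 18%.
- Counting only results in the favourable direction: 1 − 0.975^7 = 16% if independent, and 14%, 11% and 9% at the same three correlations.

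**4. What an interval would show.** The half-width of an unadjusted 95% confidence interval for the between-arm difference is t × √(2/n). At 30 per arm this is 2.002 × √(2/30) = 0.52 SD; at 24 per arm it is 0.58 SD. For comparison, the within-arm half-width at n = 30 is 2.045/√30 = 0.37 SD of change. That interval is narrower, but it is for a quantity that is not the treatment effect.

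**The case against.** Much can be said for the plan, and several stronger readings fail.

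- **The significance rule will misdirect the decision on a definitive trial.** A reader might infer this, but no section ties progression to a p-value. Section 6.1 names the pooled SD as the input for sizing the next trial, the only numerical thresholds are the feasibility and acceptability criteria of section 5.1, and section 8 commits to publishing results whichever way they fall. The p-values can mislead; the documents do not show that they will.
- **The trial has a 30% false-positive rate.** BNSS is the single primary outcome, with a rate of 5%. The 30% needs independent scales and a rule that any significant scale counts as success, and the protocol states no such rule. Unadjusted secondary outcomes are common in a pilot. What stands is that neither section 6.1 nor hypothesis 2 ranks the outcomes.
- **Only means and SDs will be reported.** The text does not say only. Intervals and multiplicity handling may sit in an analysis plan or full protocol that is not shown, so their absence here is not the fault.
- **A useful effect will usually be missed.** This is not shown for the test as written, which has 75% power at a change of 0.5 SD. Low power applies to the between-arm comparison if it were tested. For the written test the main risk is the opposite one, crediting RFCBT with change that has another cause.

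The plan's language is also largely exploratory, and stating a conventional alpha does not by itself contradict that. What survives rests on stated text: a significance criterion, on a within-arm contrast, in a study said to have no power basis and said elsewhere to compare arms.

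**Conclusion.** The concern holds in a limited form. Section 6.1 fixes a criterion that cannot separate a treatment effect from change over time, and that would be uninformative for small to moderate effects if moved to the between-arm comparison. The sizes are about 75% spurious significance on a scale where OPUS alone yields a change of 0.5 SD, and about 33% between-arm power at d = 0.4. Both rest on assumed effects, since the protocol gives none. The multiplicity figure, 18% to 30% depending on correlation, is secondary and does not apply to BNSS alone. This is a weakness in how efficacy results will be judged. It does not affect the feasibility aims or the stated use of the pooled SD.

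**What to change.** In section 6.1, replace the p<0.05 criterion on within-arm change with the baseline-adjusted between-arm difference at post-treatment and its 95% confidence interval. Report BNSS first and the six secondary outcomes as exploratory. Within-arm changes can stay as description, with means and SDs. The chi-square test named as the alternative to the paired t-test, which is not a counterpart of it, goes with the replaced sentence. State that no efficacy claim will rest on statistical significance. In section 1.2, word hypothesis 2 as an aim to estimate the effects on the named outcomes.

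No new progression rule is needed, whether based on p-values or on intervals, because the protocol has no significance rule for progression to replace. Formal multiplicity adjustment is not needed either.

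The cost is wording only, with no extra patients or data, since both arms are already assessed at both visits. The sponsor gives up the option of claiming a significant pilot result and must show an interval that will be wide: about ±0.52 SD before adjustment at 30 per arm, and narrower after it by an amount that depends on the correlation between baseline and follow-up, which the protocol does not give.

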### 2.6 Qualitative sub-study

Individual semi-structured interviews with purposefully sampled participants allocated to the experimental group will be carried out at baseline (focusing on motivation for participation) and repeated posttreatment after approximately three months (focusing on experience of participation). To ensure maximum variation, participants will be sampled according to age, gender and rumination severity, and an interview schedule including open-ended questions and probing is used to support information richness. The information power (i.e., data saturation) is assessed after interviews with 10–12 patients and additional 3–5 interviews will be conducted if needed. For patients who drop out of the intervention before the end of the intervention, the reasons for this are carefully requested. Furthermore, all participants in the intervention group are invited to a concluding group interview. Consequently, a total of three group interviews will be conducted, with a maximum of ten participants per group.”

The purpose of the group interviews is to facilitate discussion and collective evaluation among the participants Finally, interviews with the two therapists responsible for the interventions will be carried out.

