## 3. Intervention

### 3.1 Experimental group

The experimental intervention consists of group-based, manualized RFCBT that follows the principal treatment components outlined in the treatment manual developed and published by Watkins [26]. The manual has been translated for use in a Danish context [38]. The treatment comprises 11 groups-session and two individual sessions and is expected to last approximately three months. The treatment is offered as an add on to standard OPUS treatment (2-year intensive outpatient treatment). Before initiating the group sessions, an individual preparatory session (one hour) will take place. This is followed by 11 group sessions of (2 hours/once a week). The intervention ends with an individual session (one hour duration).The therapy includes review and completion of hand-outs, psychoeducation, or dissemination of important messages from the manual, practical exercises, and behavioral experiments (patients cooperate in pairs), guided visualization exercises as well as dialogue and exchange of experiences. RFCBT is based on the theoretical conception, that rumination can be seen as a mental-habit. It uses functional analysis to help people change the habits of rumination and avoidance behavior by identifying triggers and practice alternative behaviors to these cues. Guided visualization is used in the group therapy sessions to motivate and engage the participants in behavior change. The participants conduct small behavioral experiments between the sessions to test the applicability of the alternative behavior in their everyday life. A primary goal is to acquire skills so that one does not automatically fall into the habit of ruminating or avoiding. The intervention takes place in OPUS and is overseen by an experienced psychologist (experiment leader) and a co-therapist.

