### 3.2 Control group

Patients in the control group receive standard OPUS treatment and are offered the experimental intervention on completion of follow-up assessment (expected at 3 months). OPUS treatment is handled by an interdisciplinary OPUS team and consists primarily of medical treatment, psychoeducation, training in symptom management and social skills as well as family involvement/ treatment. All patients in OPUS have a contact doctor and a contact person who is responsible for coordinating the treatment and collaborating with municipal bodies.

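### RFCBT is given in therapy groups, but the named test treats RFCBT patients as independent, and the pooled SD, the only named input for sizing the definitive trial, comes with no allowance for clustering

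*Protocol article*

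**What the plan says.** Section 3.1 of the protocol article says: "The experimental intervention consists of group-based, manualized RFCBT". It describes 11 weekly two-hour group sessions, framed by one individual session before and one after, with exercises in pairs and shared discussion.

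Section 3.2 says: "Patients in the control group receive standard OPUS treatment and are offered the experimental intervention on completion of follow-up assessment". During the comparison period, therefore, only the experimental arm is grouped, although patients are randomised individually (section 2.4).

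Section 2.3 sets the numbers: "A total of 30 patients receiving the intervention will be compared to 30 receiving standard treatment". It also says that "the number of subjects is not based on a calculation of statistical power".

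Section 6.1 names a paired t-test, or a non-parametric counterpart, on change within the RFCBT arm at two-sided 0.05. It closes with the planning step: "The estimated pooled standard deviation from both groups in this pilot study will be used to inform the sample size calculation". The article mentions no therapy-group term, ICC or design effect.

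The only figures on groups are in section 2.6 and concern the closing interviews, to which all RFCBT participants are invited: "a total of three group interviews will be conducted, with a maximum of ten participants per group".

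**The concern.** Patients treated in the same group attend the same sessions and work with the same peers, so their outcomes may be positively correlated. A t-test on 30 patients assumes that they are not. If the correlation is positive, the standard error of the mean change in the RFCBT arm is too small, and the test rejects too often. The named test uses only the arm treated in groups, so the whole design effect falls on it.

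The same gap affects the pilot's forward use. A definitive trial of a group therapy needs an SD and an allowance for clustering in the therapy arm. Section 6.1 names only the SD. If the sample size were built on that alone, the later trial would have less power than intended.

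**Working it through.** **Inputs from the protocol article.** 30 patients per arm (2.3); group delivery in the RFCBT arm only (3.1, 3.2); paired t-test in the RFCBT arm, two-sided 0.05 (6.1); pooled SD as the named sample-size input (6.1).

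**Assumed inputs.** The number and size of therapy groups are not stated. Three closing interviews of at most ten give 3 × 10 = 30, the size of the RFCBT arm, which suggests three groups of about 10; five groups of 6 is the alternative. No ICC is given, so 0.01, 0.05 and 0.10 are used.

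**The plan's own figure.** The total of 60 is 30 + 30 and comes from expected recruitment, so there is no power calculation to reproduce.

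**Step 1: design effect in the RFCBT arm.** DE = 1 + (m − 1) × ICC. For m = 10: 1 + 9 × 0.05 = 1.45 and 1 + 9 × 0.10 = 1.90. For m = 6: 1 + 5 × 0.05 = 1.25 and 1 + 5 × 0.10 = 1.50. The true standard error is √DE times the independence value, and the effective sample size is 30/DE.

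**Step 2: type I error of the paired test.** Simulated with 60,000 replicates per setting and no true change. At ICC 0 the simulation returns 0.048–0.049, as it should.

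**Step 3: size of a later 1:1 trial.** Only one arm is clustered, so total N is multiplied by (DE + 1)/2. Inflating the RFCBT arm alone by DE gives the same total: n + n × DE = 2n × (DE + 1)/2.

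| Groups (assumed) | ICC (assumed) | DE | √DE | Effective n of 30 | Type I error | (DE + 1)/2 |
|---|---|---|---|---|---|---|
| 3 × 10 | 0.01 | 1.09 | 1.04 | 27.5 | 0.059 | 1.045 |
| 3 × 10 | 0.05 | 1.45 | 1.20 | 20.7 | 0.103 | 1.225 |
| 3 × 10 | 0.10 | 1.90 | 1.38 | 15.8 | 0.155 | 1.45 |
| 5 × 6 | 0.01 | 1.05 | 1.02 | 28.6 | 0.057 | 1.025 |
| 5 × 6 | 0.05 | 1.25 | 1.12 | 24.0 | 0.078 | 1.125 |
| 5 × 6 | 0.10 | 1.50 | 1.22 | 20.0 | 0.109 | 1.25 |

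**Step 4: an illustration.** Assume a standardised difference of 0.5 and 80% power. Under independence, n = 2 × ((1.960 + 0.842)/0.5)² ≈ 62.8, so 63 per arm. With groups of 10 this becomes 66, 77 or 92 per arm at ICC 0.01, 0.05 or 0.10. Left at 63, power is 78%, 72% or 64%. With groups of 6 it becomes 71 or 79 at ICC 0.05 or 0.10, and power at 63 is 75% or 71%.

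**Step 5: is the pooled SD itself wrong?** The expected RFCBT-arm variance is σ² × [1 − ICC × (m − 1)/(n − 1)]. With m = 10, n = 30 and ICC 0.10 this is 1 − 0.10 × 9/29 = 0.969 σ². Averaged with the control arm it is 0.984 σ², so the SD is 0.992 of the true value; at ICC 0.05 it is 0.996. In the illustration this moves n by at most one, from 63 to 62. The shortfall comes from the absent design effect, not from the SD.

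**The case against.** The strongest reply has five parts.

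- **The later trial is not yet designed.** A reader might infer that it will be undersized. The article does not support that: the SD is to inform the calculation, and nothing excludes adding a design effect from outside data. This stands, so the shortfall is conditional.
- **Group structure is inferred and the ICC assumed.** A reader might take section 2.6 to say that there are three therapy groups of ten, but it describes interviews. This stands too. At ICC 0.01 the effect is small, and at zero there is none. With smaller groups the effect shrinks but does not vanish.
- **Therapists may add nothing.** A reader might count a shared therapist as a source of correlation. Section 2.6 says "interviews with the two therapists responsible for the interventions will be carried out". If the same two run every group, the therapist is constant across groups and adds no between-group variance. The concern rests on shared sessions and peers only.
- **This is an exploratory pilot.** Its N is not power-based, and section 10 leaves confirmation to a later trial. That limits the harm of an inflated type I error here, but not the relevance to planning the later trial.
- **An article may leave detail to a fuller document.** True in general, but section 6.1 itself states both the test and the planning input, and the point concerns what is stated there.

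Separately, the Abstract promises a between-arm comparison of change that section 6.1 does not specify. That is a different matter. In such a comparison the variance would be inflated by (DE + 1)/2 rather than DE.

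**Conclusion.** The point holds in a limited form. The named test ignores clustering in the only arm that has it, and the one named input for sizing the definitive trial carries no allowance for it.

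Under any positive ICC the RFCBT-arm standard error is too small. At ICC 0.05–0.10 it should be 1.20–1.38 times larger with three groups of 10, or 1.12–1.22 times with five groups of 6. The type I error is then about 0.10–0.16 or 0.08–0.11. A definitive trial sized on the SD without a design effect would need 22.5–45% or 12.5–25% more patients respectively.

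These figures depend on assumed group sizes and ICCs. The article does not show that the pooled SD is biased, nor that the later trial is bound to be too small. This is an inexpensive improvement rather than a flaw that undermines the pilot.

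**What to change.** 1. Record a therapy-group identifier for every RFCBT patient, and report the number and size of the groups.
2. Report effect estimates with confidence intervals widened for assumed ICCs of, for example, 0.01, 0.05 and 0.10, by multiplying the RFCBT-arm variance term by 1 + (m − 1) × ICC. A few groups cannot estimate an ICC, so a partially nested mixed model (random group effect in the RFCBT arm only, small-sample degrees of freedom) should be a sensitivity analysis only.
3. Change the last sentence of section 6.1 to say that the definitive sample size will use the pooled SD together with a design effect of 1 + (m − 1) × ICC for the RFCBT arm, over a stated and justified ICC range, with m the group size planned for that trial.

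The cost is one extra data field and a few lines of analysis text, wider confidence intervals in the pilot, and a larger N for the definitive trial. The pilot needs no extra patients or visits.

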### 6.2 Qualitative analysis

Data from individual interviews as well as group are analyzed using systematic text condensation or equivalent data-driven thematic analysis [46]. All analyzes are carried out in collaboration between several researchers (researcher triangulation) and using NVivo software for qualitative data analysis. A minimum of three members of the research team will be involved in the analysis of the qualitative data. The involved researchers will have diverse educational backgrounds (clinical psychologist, nursing), thereby being able to contribute with different perspectives in the interpretation of data (i.e., researcher triangulation) to enhance rigor and trustworthiness. Specifically, two researchers will independently code the transcribed interviews and meet with a third researcher to discuss development of higher-order themes.

